## **1. Summary**

Correct prescription, dispensing and administration of drugs are crucial for safe pharmacotherapy. In hospitals, almost every fifth drug dose is administered erroneously. It is supposed that at home, where patients or family caregivers are responsible for correct drug administration, error rates are even higher. Patient education on correct medication administration increases adherence and safety of administration. When comparing different educational interventions, it became evident that they differ significantly in their effectiveness. Training that addresses the individual needs of the patient is more effective than interventions that provide general information. A previous focus group study with patients, family caregivers, and nurses (ethics vote S-206/2013), which aimed at determining drug administration problems, revealed that many medicine users were unaware of drug administration errors. To address the lack of error awareness, the Transtheoretical Model developed by James D. Prochaska and his colleagues provides a theoretical framework. This model involves five different levels that a person goes through when he intrinsically changes his behavior. Studies to improve compliance show that level-specific measures, according to the Transtheoretical Model, positively influence the outcome of an intervention. Therefore, this prospective randomized controlled study, aims to evaluate standardized patient education in community pharmacies. This study takes into account the possibly lacking error awareness of the patient or family caregiver and feasibility in community pharmacies. Pharmacy staff will be trained on the study procedure, use of study material and correct administration of different dosage forms. Subsequently, pharmacy staff includes patients during their daily routine into the study. In a before and after comparison of the intervention group with the control group and follow-up visits, the effectiveness and sustainability of patient education will be evaluated

[figure not shown]

### 3. Introduction

The ideal pharmacotherapy does not only depend on choosing the right drug but also on an assured quality of prescription, dispensing and application. Notably incorrect medication administration therefore poses a current problem regarding safety of drug therapy [1-3]. At hospitals almost every fifth dose is administered incorrectly [1,2], either decreasing the efficacy of pharmacotherapy [4-7] or increasing the risk of an adverse drug event [3,4,8]. Out of hospital, it is rarely the ambulatory nursing service but more often the patient himself or family caregivers who are responsible for the medication administration. Thus, one can assume that in daily usage of drugs at home, the amount of incorrectly administered doses is even higher [9-11]. If the patient is overstrained due to medication administration this will frequently cause non-adherence [12,13]. Interventions (based on different training methods) for the correct administration of drugs could increase medication adherence and safety in patients and family caregivers as well as in health care professionals [14,15]. Comparing different training methods, it is shown that their effectiveness can differ noticeably [16]. Hereby, trainings considering individual patient's needs are more effective than methods educating more general information [16].

In a previous focus group study (ethics vote S-206/2013) for patients, family caregivers and nursing staff focusing on registration of medication administration problems in daily life and on determination of training requirements, it is shown that a lot of medicine users are not aware of possible errors [[name] et al., unpublished]. In fact, patients often feel a lot better informed than they really are [17]. In a study about the correct application of eye drops, 93 % of the patients reported not to have problems with the application though this was indeed true for less than a third of the patients [18]. Just as 94 % of COPD patients overestimated their skills of administering their inhaler correctly [19]. The lack of error awareness makes it difficult to motivate such patients participating in training or a detailed consultation. The Transtheoretical Model developed by James D. Prochaska and his colleagues delivers the theoretical framework for considering the initially missing awareness for the problem on the way to change the behavior [20,21]. The Transtheoretical Model mainly includes five different levels a person will undergo if he or she changes his or her behavior [20]:

- Level 1: During the unintentional state (“Pre-contemplation”) persons do not follow the intention to change problematic behavior.
- Level 2: During the state of establishing intention (“Contemplation”) persons follow the intention to change problematic behavior eventually.
- Level 3: During the state of preparation (“Preparation”) persons plan precisely to change their problematic behavior soon and take first steps to the direction of altering their behavior.
- Level 4: During the state of action (“Action”) persons change their behavior.
- Level 5: During the state of maintenance (“Maintenance”) persons have given up their problematic behavior for a longer period of time.

With methods respecting the individual level of the patients or family caregivers, progress to change their behavior may be positively influenced [20]. Thus, studies for improving the compliance show that considering the individual levels influences the outcome of the intervention positively [21]. The model has not been applied yet for trainings to avoid medication errors. Yet it seems to be obvious that patients or family caregivers, who do not realize a medication error because they have not been aware of it, do not recognize the necessity for training. To reach these patients and family caregivers and to motivate them for training, the Transtheoretical Model could be the theoretical framework for implementing training interventions.

According to this prospective randomized controlled study, standardized patient education in community pharmacies should be evaluated. The training method should consider the patients’ or family caregivers’ lack of awareness if necessary and particularly should be integrated in the daily routine of pharmacies. For this reason, the pharmacy staff of the particular community pharmacy will carry out the training and document any additional work required. Before the study is started, the pharmacy staff will be informed about incorrect and correct administration of the dosage form which is known from literature (see inclusion criteria), the use of education materials and the study procedure. There are three follow-up visits planned, approximately one month, six months and twelve months after the first patient education. Patients or family caregivers will either be addressed in the community pharmacy (recruiting and follow-up visits) or they will be contacted by employees of the participating community pharmacies or by an employee of the department of Clinical Pharmacology and Pharmacoepidemiology and they will

be invited into the correspondent community pharmacy (follow-up visits). The pharmacy staff or employees of the department of Clinical Pharmacology and Pharmacoepidemiology will again assess the quality of medication administration of patients or family caregivers during their follow-up visits to evaluate the sustainability of the first training.

#### **4. Aims and issues of the project**

##### **Primary outcome**

- Rate of incorrect medication administration will be compared between control and intervention group at 6-month follow-up.

##### **Secondary outcomes**

- Rate of incorrect medication administration before and after patient education in the control and intervention group.
- Rate of incorrect medication administration during the course of follow-up visits.
- Influence of the consideration of the individual level according to the Transtheoretical Model [20] on the willingness to participate in a training, i.e. long-term (1, 6 and 12 months) correct drug use.
- Univariate and multivariate analyses to evaluate the influence of covariates such as dosage form, patient characteristics, the training person and the number of medicines on training success.
- Qualitative: feasibility of implementation in community pharmacies, satisfaction of patients and caregivers.

##### **The following general questions are related to the project:**

- Is it possible to motivate patients or family caregivers to attend training by raising awareness of a drug administration error?
- Is the consideration of the individual awareness of the error an advantage in the training compared to a "normal" counseling?
- Is the training success sustainable?
- Is the patient education intervention feasible in the community pharmacy setting?
- Are any differences in training success depending on the dosage form or person?

## **5. Method to be tested**

### **General description**

The influence of the individualization of patient education on the success of the training should be evaluated.

### **Effects/risks**

Adverse events due to participation in the study are not expected. If relevant issues outside of drug use are identified in individual cases, assistance and advice on specific issues will be provided by pharmacy staff. If a misuse of the drug occurs during the trial, pharmacy staff will inform the patient or caregiver of the error and the correct application.

## **6. Study design**

Prospective, cluster-randomized, controlled interventional study.

## **7. Planned sample size**

See statistical analyses

## **8. Inclusion criteria**

Patients and family caregivers:

- Age >18 years
- Physical and cognitive ability to attend training
- Application of at least one of the following dosage forms to oneself or others: Eye drops, transdermal patches, tablets to divide, liquid oral preparations and/or capsules
- Written informed consent to study participation after oral and written clarification

Pharmacy staff:

- Written informed consent to study participate in the study after clarification in a written or oral form

Community pharmacies:

- Spatial requirements to enable confidential consultation

[figure not shown]

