## **9. Exclusion criteria**

Minors or persons who are not able to give their consent or who are physically or cognitively unable to attend training or understand German education are excluded. Also excluded are study participants (patients, caring family members and pharmacy staff) who do not give or withdraw their written informed consent.

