## **11. Study procedure**

The study will be carried out in community pharmacies with which other projects have already established cooperation. Prior to the start of the study, pharmacy staff will be informed of erroneous and correct administration of the different dosage forms (see inclusion criteria) known from the literature, the use of study materials, and the study procedure. After written informed consent of the head of the pharmacy and pharmacy staff, the pharmacies will be assigned to control or intervention group (cluster randomization). There will be exclusive control pharmacies and intervention pharmacies.

Pharmacy staff addresses potential study participants according to the inclusion criteria during daily routine in the community pharmacy. It is possible within the scope of this study to train the use of different dosage forms for the same patient or family caregiver. In order to identify a potential administration error, the pharmacy staff asks the patient or family caregiver to use the medicine (duration approx. 2-5 minutes). Such a demonstration is quite common in the context of the usual pharmaceutical counseling. The demonstration can be performed with the patient's drug itself or with a placebo. The pharmacy staff assesses a possibly incorrect administration by using a checklist defined in advance for a specific dosage form. Checklists and placebo materials are provided by the Department of Clinical Pharmacology and Pharmacoepidemiology. In the control group, pharmacy staff provides a standard consultation (duration approx. 3 minutes) followed by the provision of standardized information material, e.g. written step-by-step

instructions. In the intervention group, the staging algorithm (Fig. 1) is used to determine the individual level of the patient or caregiver according to the Transtheoretical Model. The stage "Maintenance", i.e. the permanent correct use of the drug, cannot be detected with this algorithm. The purpose of this model is to identify in particular those medicines users who are not aware of administration errors despite incorrect use of the drug and who may not be motivated to seek training or detailed counseling.

[figure not shown]

Figure 2. Staging Algorithm

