| Maintenance | Drug is permanently administered correctly | e.g. regular monitoring                                         | Follow-up visits with re-presentation of the application and assessment by the pharmacy staff             |

Immediately after the training (intervention group) or after issuing the standardized instructions (control group), the drug application is checked again using the checklist. If errors continue to occur, there will be a corresponding retraining in the intervention group. In the control group, the patient or family caregiver is made aware of the errors verbally.

After the pharmaceutical consultation that can represent a standard situation in community pharmacies, the patients or caregivers are invited to participate in the follow-up visits. Study information is provided by the pharmacy staff or staff of the department of Clinical Pharmacology and Pharmacoepidemiology. If the patient or caregiver wishes to participate in the study and attests this by his written consent, his so far anonymized data will be pseudonymized. After inclusion in the study, patients and caregivers are asked to answer a sociodemographic questionnaire (duration approx. 5 minutes). In addition, e.g. finger strength and cognitive abilities may be considered as factors influencing the training success. Further data collection during follow-up visits is pseudonymized. Within the study, three follow-up visits will be planned at 1 month, 6 months and 12 months. Patients or caregivers are either referred to the follow-up at the pharmacy at the appropriate time or contacted by pharmacy staff or staff of the department of Clinical Pharmacology and Pharmacoepidemiology. Patients or caregivers can choose the preferred way of contacting, e.g. call, email or letter, prior to inclusion into the study. At follow-up visits the patient or family caregiver will be asked to demonstrate again drug administration, which is evaluated by the pharmacy staff or staff of the department of Clinical Pharmacology and Pharmacoepidemiology using the checklist. In the case of incorrect application, re-training takes place again. During the follow-up visits, patients and caregivers might be contacted by pharmacy staff or staff of the department of Clinical Pharmacology and Pharmacoepidemiology, e.g. by

[figure not shown]

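### Staff who know their pharmacy's arm choose whom to approach, using an ability criterion worded around training, so screening can differ between arms before any counselling

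*Protocol*

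**What the plan says.** Protocol section 8 lists "Physical and cognitive ability to attend training" as an inclusion criterion. Section 9 mirrors it: persons "physically or cognitively unable to attend training or understand German education are excluded". Neither section gives a test or threshold for ability.

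Section 11 sets the order of events. Pharmacies come first: "After written informed consent of the head of the pharmacy and pharmacy staff, the pharmacies will be assigned to control or intervention group". Each pharmacy then works in one arm only: "There will be exclusive control pharmacies and intervention pharmacies". Recruitment follows: "Pharmacy staff addresses potential study participants according to the inclusion criteria during daily routine in the community pharmacy".

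The arms differ in what happens next. "In the control group, pharmacy staff provides a standard consultation (duration approx. 3 minutes"), followed by written material. Intervention users are staged and, if in a pre-action stage, receive level-specific training of about 5 to 10 minutes. The repeat check is timed "Immediately after the training (intervention group) or after issuing the standardized instructions (control group"), and if errors persist "there will be a corresponding retraining in the intervention group", while controls are told of their errors verbally.

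Invitation to follow-up and consent come after the counselling (sections 11 and 16). Section 11 also says that finger strength and cognition may be taken into account as influences on training success, and places this after inclusion. Section 15 compares the groups' error rates by a chi-square test.

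**The concern.** In a cluster-randomised trial that recruits individuals after allocation, randomisation balances the pharmacies but not the people each pharmacy brings in. Here the recruiters also deliver the arm's procedure, so they must know the arm, although the protocol does not say so in words. They select during routine work. The document states no consecutive-approach rule and no record of who was passed over.

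The ability criterion adds a specific route. It reads the same in both arms, but staff may apply it with their own arm's session in mind: a consultation of about 3 minutes, or staged training of 5 to 10 minutes with possible retraining. A customer with limited dexterity or cognition could be judged able in one pharmacy and unable in another. If ability also affects correct use at 6 months, part of the between-group difference would reflect who was approached and not what they were taught.

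**Working it through.** **Sequence.** Taken from sections 8, 9, 11 and 16:

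1. Pharmacy staff consent and the pharmacy is allocated.
2. Staff approach customers and apply the ability criterion.
3. The customer demonstrates use of the medicine and is scored on the checklist.
4. Training or standard consultation is given, then a second check.
5. The customer is invited to follow-up and consents.

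The selection discussed here is at step 2. Step 5 is a further selection point, and changing its timing would not affect step 2.

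**Number for the illustration.** Section 15 gives success rates of 32% and 52%, alpha 0.05, 80% power (printed as beta), 15% drop-out and ICC 0.02. Sidedness is not stated; two-sided is taken. The usual two-proportion formula without continuity correction gives

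n = [1.96·√(2·0.42·0.58) + 0.842·√(0.32·0.68 + 0.52·0.48)]² / 0.20² = 94.4, so 95 per group.

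The plan's own figures follow:

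- 95 × (1 + 4 × 0.02) = 102.6 → 103; 103 / 0.85 = 121.2 → 122.
- 95 × (1 + 9 × 0.02) = 112.1 → 113; 113 / 0.85 = 132.9 → 133.

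Both match section 15, with 5 and 10 entering as users per pharmacy. Whether that is the right use of those numbers is a separate question. Here 95 serves only as the effective number per group that the plan intends to have.

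**Bias.** Let s be the share of otherwise eligible customers judged unable in one arm's pharmacies only, and g the amount by which their success at 6 months falls short of the others'. The arm that keeps them has success lower by s × g. Neither quantity is in the protocol; the values are assumptions.

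| s | g (points) | bias = s × g (points) |
|---|---|---|
| 0.10 | 15 | 1.5 |
| 0.15 | 20 | 3.0 |
| 0.20 | 30 | 6.0 |

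**Consequence.** With d = p₂ − p₁, p̄ the mean of the two rates, s₀ = √(2p̄(1−p̄)/95) and s₁ = √([p₁(1−p₁) + p₂(1−p₂)]/95), the two-sided rejection probability is

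1 − Φ((1.96·s₀ − d)/s₁) + Φ((−1.96·s₀ − d)/s₁).

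Example, 32% against 38%: s₀ = 0.0692, s₁ = 0.0691, 1.96·s₀ = 0.1356. The upper tail is 0.1367 and the lower 0.0023, together 13.9%.

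| bias (points) | no true effect, bias favours intervention | true +20 points, bias against intervention |
|---|---|---|
| 0 | 5.0% (32% v 32%) | 80% (32% v 52%) |
| 1.5 | 5.6% (32% v 33.5%) | 74% (32% v 50.5%) |
| 3.0 | 7.2% (32% v 35%) | 67% (32% v 49%) |
| 6.0 | 13.9% (32% v 38%) | 51% (32% v 46%) |

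Wider assumptions give wider results. If the share of able users differs by 10 to 30 points between arms and success differs by 20 to 40 points between more and less able users, the bias is 2 to 12 points (0.10 × 20 to 0.30 × 40). The protocol does not help choose between these ranges.

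**The case against.** A reader might infer that training is given in the intervention arm only, so that the criterion has no meaning for controls. The document does not support that. The contrast holds at first contact. Re-training for errors at follow-up visits is not restricted to one arm, the secondary outcomes in section 4 speak of patient education in both groups, and sections 15 and 16 use training without naming an arm. The criterion can fairly be read as one common entry rule.

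A reader might also infer that people are enrolled before counselling. They are not: invitation and consent come afterwards, and only approach and screening come before. Nor does the criterion allow staff to pass over someone merely in a hurry, since it concerns physical and cognitive ability.

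A third tempting reading is that the bias must favour the intervention. Section 11 says the staging model is meant to find users unaware of their errors, so intervention staff might equally seek out customers who seem to need more help. That would work against the intervention.

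It can further be said that both arms require the same demonstration, that the initial checklist would show an imbalance in starting skill, and that patient characteristics enter a logistic regression. This stands in part. The initial checklist covers only people already approached and cannot show who was passed over. Section 15 describes the regression as a study of influences on education success, not as the group comparison. Further adjustment may be set out in an analysis plan that is not at hand, but no adjustment recovers a record of people never approached.

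Finally, recruitment by staff who know the arm would be a risk whatever the criterion said. That is correct, and it is why the approach rule matters more than the wording.

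**Conclusion.** The point holds as a risk of differential approach and screening after allocation. It rests on the stated order of events, on single-arm pharmacies whose staff both recruit and deliver, on an untested ability judgement whose wording coincides with the intervention's content at first contact, and on an unadjusted primary comparison. Knowledge of the arm is inferred from staff delivering it. The document contains no instruction to apply the criterion differently and no evidence that this will happen.

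The size is illustrative only. At the low end of the assumed range the false-positive rate is practically nominal (5.6%); at 6 points, under a third of the planned 20, it is about 14%, or power is about 51% if the bias runs the other way. These figures assume 95 effective observations per group, a two-sided test and 32% control success, and they depend directly on the assumed share and gap. The protocol should be amended because the change is cheap and, as written, the selection would go unrecorded.

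**What to change.** In section 11, require staff in both arms to approach consecutive customers with a listed dosage form during the same pre-set recruitment periods. Have every pharmacy keep an anonymous tally of those approached, judged unable and declining, so that the arms can be compared at each step.

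In sections 8 and 9, replace the reference to training with a criterion that places the same demand on both arms, for example: able to carry out the observed demonstration, which both arms require, and to understand instructions in German.

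The cost is a short amendment, a tally sheet and some loss of staff discretion over whom to approach. Endpoint, sample size and counselling content stay as they are. The change narrows the room for selection and makes it visible; it does not remove the risk that comes with unblinded recruitment after allocation.
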